#### Sample Size Justification

The sample size calculation is powered to detect the primary outcome, which is the change in HbA_1c_. Reviews of published studies suggest that successful education programs lower A_1c_ levels by 0.4% to 1.7% [3,103]. On the basis of our previous experience with the patient population, we estimated a mean baseline HbA_1c_ level of 10% with a SD of 1.8 and an effect size of 0.56 for aim 1. The cross-time correlation was estimated to be 0.30, with a compound symmetry structure. We adjusted for clustering and assumed an intraclass correlation coefficient of 0.01, with 5 clusters. This yielded a design effect of 1.34. Two-sided alpha of .05 and 80% power were assumed. Allowing for a 20% dropout rate, 220 patients were required [104].

#### Data Management and Analysis

To address missing data, we will examine the data for patterns of missingness and potential bias in missingness. If data are not missing at random, we will apply one of several available imputation methods in a sensitivity analysis based on the nature and extent of missing data [105]. We will determine effectiveness using intention-to-treat principles with actual imputation of missing data [106-109]. This will allow us to appreciate the potential biases inherent in a *real-world* setting due to dropout and poor adherence to study procedures.

Patients who share a single PCP might exhibit similarities that are not shared with patients cared for by other PCPs. To address this, we will include random effects in the model for clinic site, PCP, and HC (though the small numbers of HCs may call for a fixed effect approach or *insufficient replication*) [110]. To examine a stricter examination of effect, we will also do a *per-protocol* analysis of complete cases. Completed cases will not be dependent on intermediate time point data collections (6 and 18 months). Potential selection bias will be corrected by including model covariates that are differentially related to study participation.

Univariate comparisons between the 2 study groups for outcomes and covariates at baseline will be conducted using chi-square tests for categorical variables, Kruskal-Wallis tests for ordinal variables, and *t* tests for continuous variables. All tests will be two-sided. Nonnormal continuous data will be transformed before the analysis. To provide a comprehensive analysis of our primary hypothesis, we will extend the usual analysis of crossover designs [111] by including a longitudinal trend component in the first year. Thus, we can examine the time course (0, 6, and 12 months) as linear or quadratic over the first 3 measurements. This will allow us to investigate whether changes are made early and at what rate they continue throughout the rest of the period. This analysis permits a comparison of the trends between the 2 conditions. In addition, we will regard subjects as a random effect and will use Gaussian mixed model estimation. We can then substitute treatment by period interactions for the carry-over effects, and the model can be reduced in a recommended sequence (first omit carry-over, then omit treatment, and finally omit period) [111]. We will also explore patterned covariance structures such as compound symmetry and autoregression along with incorporating time-constant and time-varying covariates, such as health literacy or diabetes distress.

The primary analysis of all physiological outcomes jointly in the repeated measures design will be conducted using a general linear model framework. Repeated measures multivariate analysis of variance will be used to explore the simultaneous impact of the treatment on multiple correlated dependent variables, including the use of Roy-Bargmann stepdown *F* tests and discriminant function analysis as post hoc tests to identify subsets of outcome measures affected [112]. Multivariate analysis of variance (MANOVA) secondary analyses will explore the impact of inhomogeneous baseline variables on the results. Group by time-trend interaction contrasts will be used to explore different group trajectories of change. The potential consequences of medication intensification (eg, initiation of insulin) will be explored by evaluating changes in BMI and quality of life.

Exploratory subgroup analyses will follow a heterogeneity in treatment effects framework [113,114]. We will determine which subjects in the intervention group had the greatest improvement in outcomes, based on multiple prespecified patient characteristics, including race (African-American or Latino), depression, comorbidities, baseline behaviors, health literacy, continuity of care, and social support. These analyses will also consider additional comparisons between subjects above and below the median levels of videoconferencing and text messaging activity. Statistical tests will be implemented as interactions within the full data set.

If the intervention results in improved HbA_1c_ more than that in the usual care, we will examine whether changes in self-efficacy, health beliefs, or social support serve as mediators for improved outcomes. In addition, we will explore diabetes-related behaviors as well as medication treatment intensification as mediators using MPlus [115-118]. To further identify the relative contributions of videoconferencing and/or text messaging, we will conduct meditational modeling with videoconferencing time, number of text messages, and HC contact time as mediating variables. This may describe any dose-response relationship between mHealth utilization and outcomes. We will compute bias-corrected bootstrap standard errors using MPlus. This offers accurate confidence intervals for mediation coefficients [119]. Due to anticipated relationships between HC activity level and mHealth delivery, we plan to inspect correlations between mediators and incorporate any significant findings in model development. This analysis will demonstrate whether the intervention effects are sensitive to mediators. Finally, given the sample size, observed (rather than latent) variables will be used in the mediation models. To enhance the power of mediation modeling, we adopt an α=.10 type I error criterion to improve the chances of finding promising mediators for future studies.

We expect a limited amount of decline in physiologic outcomes with the transition back to usual care. We will test the hypothesis that improvements in HbA_1c_ (primary outcome), blood pressure, and LDL cholesterol (secondary outcomes) will be maintained during the maintenance period. The analyses will be conducted in a manner similar to our primary hypothesis and will evaluate changes in the initial intervention group 1 year after intervention completion.

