### Objectives

The aim of this study is to evaluate the impact of an mHealth clinical pharmacist and HC intervention in African-Americans and Latinos with poorly controlled type 2 diabetes. We hypothesize that the mHealth intervention will improve HbA_1c_, blood pressure, and low-density lipoprotein (LDL) as well as medication and lifestyle behavior adherence compared with usual care. In addition, the crossover design will test the hypothesis that improvements in outcomes resulting from the intervention in year 1 will be maintained during the maintenance period (usual care) in year 2.

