**Figure 1 figure1:**
[figure not shown]
Randomized crossover study design.

The primary outcome is the change in HbA_1c_ level. Secondary outcomes include changes in blood pressure and LDL cholesterol levels. Using a 1:1 ratio, we will randomize 220 patients to either (1) a mHealth intervention delivered by a clinical pharmacist and HC for 1 year, followed by usual care for 1 year, or (2) usual care for 1 year, followed by the mHealth intervention for 1 year. Both groups will crossover at the end of year 1, such that those receiving the mHealth intervention during the first year will receive usual care during the second year (to evaluate potential maintenance of outcome improvement). Similarly, those with usual care in year 1 will crossover to receive the intervention in year 2 (to ensure that all subjects are able to receive the intervention). Of note, we do not consider HbA_1c_ levels collected at the end of year 1 when crossover occurs. The treatment received by patients (intervention or usual care) will change at the end of year 1, independent of HbA_1c_ levels.

Separate randomization schedules generated in REDCap will be used for each of the 4 main clinical sites with stratification for ethnic group (African-American and Latino) and gender to balance the proportion of participants across randomized conditions. All study procedures have been approved by the University of Illinois at Chicago Institutional Review Board (IRB 2016-0380).

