Home visits include the HC and patient. Family members are permitted by patient requests. Through open discussion and reflective listening, HCs encourage patients to explore their emotions and share their concerns [83]. Overall, HCs provide diabetes self-management education and support (DSME/S), consistent with the recommendations of the American Diabetes Association’s position statement [83]. Specifically, HCs provide DSME/S that includes the following over the course of the 1-year intervention: engagement, information sharing, psychosocial and behavioral support, integration with other therapies, and coordination of care. Initial HC encounters focus on relationship building and gaining an understanding of the patient’s individualized diabetes education needs. HCs provide diabetes education and consider realistic and achievable food choices, portion sizes, and cooking preparation; discuss relationships between medications, meals, and glucose levels; and help patients integrate movement into their daily lifestyles. Diabetes education is facilitated by our culturally appropriate multimedia education iBook, *Living Well with Diabetes/Viviendo Bien con Diabetes* [84]. This iBook (available in English and Spanish) provides patients with video testimonials and various interactive educational experiences. HCs present specific chapters on an iPad to reinforce specific diabetes self-management concepts [84]. To promote behavioral change, HCs use motivational interviewing techniques to assist patients in setting specific health behavior change goals. Goals set jointly by HCs and patients follow the specific, measurable, achievable, relevant, and time-specific (SMART) framework [85]. Providing social support while helping patients engage with their existing support systems offers the potential of long-term behavior change beyond the duration of the research period. Educating patients on how to effectively navigate the health care system and use existing resources promotes continued self-efficacy. In summary, HC interactions are culturally tailored to individual needs, preferences, and resources to provide DSME/S [86].

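### The crossover model for the primary hypothesis may drop its carry-over term first, although the trial expects the year-1 effect to persist, so the pooled estimate would depend on how much effect is maintained

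*Protocol article*

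**What the plan says.** Study Design: "Using a 1:1 ratio, we will randomize 220 patients" to intervention then usual care, or the reverse, one year each. "Both groups will crossover at the end of year 1", and no washout is described. The reasons given for crossing over are to evaluate maintenance and to let every participant receive the intervention. "The primary outcome is the change in HbA_1c_ level"; the article does not say whether year-2 change is counted from month 0 or month 12.

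Objectives: the design is to test whether "improvements in outcomes resulting from the intervention in year 1 will be maintained during the maintenance period (usual care) in year 2". Data Management and Analysis adds that only limited decline is expected after the return to usual care. The HC section says that the social support provided "offers the potential of long-term behavior change beyond the duration of the research period".

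Data Management and Analysis: the primary hypothesis is analysed by extending the usual crossover analysis with a time trend over months 0, 6 and 12. Treatment-by-period interactions may stand in for carry-over, and "the model can be reduced in a recommended sequence (first omit carry-over, then omit treatment, and finally omit period". No test, threshold or other criterion is given. The same section also calls a joint analysis of all physiological outcomes primary.

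**The concern.** An effect that is maintained after the switch is carry-over. The plan therefore expects carry-over and lists it as the first term that may go. Without the term, year 2 compares patients who may still hold the year-1 benefit with patients newly receiving the intervention, and the model averages that contrast with the clean year-1 contrast. The resulting treatment effect then mixes efficacy with persistence, and the article does not name the year-1 comparison as the estimate that takes precedence.

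A second issue follows if the term is dropped on a significance test. In a two-sequence design, carry-over is tested between patients and with low precision, so a real carry-over can be missed. Choosing the estimator from that test also disturbs the type I error.

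**Working it through.** **The plan's own figures** (Sample Size Justification: SD 1.8, effect size 0.56, correlation 0.30, ICC 0.01, 5 clusters, 20% dropout, two-sided 5%, 80% power).
- Completers: 220 × 0.8 = 176, or 88 per arm.
- Design effect: 1 + (176/5 − 1) × 0.01 = 1.342, matching the stated 1.34.
- Sample size, reading 0.56 as SD units and comparing change from baseline in two arms: 4 × (1.960 + 0.842)² × 2(1 − 0.30) / 0.56² ≈ 140.2 in total. Then 140.2 × 1.34 ≈ 187.8. Multiplying by 1.2 gives about 225; dividing by 0.8 gives about 235. The stated 220 is only loosely reproduced.

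**Bias if carry-over is omitted.** Let τ be the treatment effect, π the period effect and λ = fτ the carried-over effect.

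| Sequence | Year 1 | Year 2 |
|---|---|---|
| Intervention first | τ | π + λ |
| Usual care first | 0 | π + τ |

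On level or change from month 0, the crossover estimate is ½[(τ − π − λ) − (0 − π − τ)] = τ − λ/2 = τ(1 − f/2).

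If year-2 change is taken from month 12, the year-2 entries become π + λ − τ and π + τ. The estimate is ½[(2τ − π − λ) + (π + τ)] = (3τ − λ)/2.

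| f | Level, or change from month 0 | Year-2 change from month 12 |
|---|---|---|
| 0 | 1.00τ | 1.50τ |
| 0.5 | 0.75τ | 1.25τ |
| 0.75 | 0.625τ | 1.125τ |
| 1 | 0.50τ | 1.00τ |

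The article does not say whether 0.56 is in SD units or HbA1c points. At f = 1 in the middle column, 0.56 SD (0.56 × 1.8 = 1.008 points) would be estimated as 0.504, and 0.56 points as 0.28. The month-12 between-arm comparison contains no λ and estimates τ in full.

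**How often a test would catch it.** Assumptions: the term is dropped when a 5% or 10% test is not significant; 88 per arm; SD 1.8; correlation 0.30; one value at the end of each period. The carry-over contrast is the between-sequence difference in patient totals:
- SE = 1.8 × √[4(1 + 0.30)/88] = 0.438.
- λ = 1.0 point: z = 2.29; detected in about 63% (5% test) or 74% (10% test).
- λ = 0.45 point: z = 1.03; detected in about 18% or 27%.

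Using two values per period and adjusting for baseline, with the full effect assumed present by months 6 and 18:
- Variance of the adjusted four-visit mean: 1.8² × [(1 + 3 × 0.30)/4 − 0.30²] = 1.247. SE of the contrast: √(2 × 4 × 1.247/88) = 0.337.
- λ = 1.0 point: about 84% or 91% (73% or 82% after the design effect).
- λ = 0.45 point: about 27% or 38%.

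**Test-then-choose as a whole** (simulated with period-end values; year-1 estimate used when carry-over is significant). At full persistence the average estimate is about 0.89τ to 0.94τ for 1.0 point and 0.71τ to 0.79τ for 0.45 point. Type I error under the null is about 7% to 8% instead of 5%.

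**The case against.** The strongest reply has four parts.

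1. **The wording is permissive.** The model can be reduced; nothing says that it will be, or on what test. This stands. A reader might infer that the trial's type I error is 7% to 8%, but that belongs to an assumed pre-test, and a criterion may be in an analysis plan that is not shown. What remains is that the article itself fixes the order of removal and puts carry-over first.

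2. **A clean comparison is already planned.** The year-1 trend over months 0, 6 and 12 is free of carry-over and compares the two conditions. This stands and makes the remedy small. It does not settle the matter, because the article presents that trend as an extension of the crossover model and does not name it as the primary estimate.

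3. **The direction depends on the reference point.** A reader might infer that the better the effect is maintained, the more the primary result shrinks, or that it will be halved. The documents do not support either without conditions. Shrinkage holds for level or change from month 0; with month 12 as reference the error is upwards and vanishes at full persistence. Halving is a bound.

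4. **The pre-test is less weak than period-end values suggest.** With all planned visits, a full carry-over of 1.0 point would usually be found, and the average over test-then-choose is well above 0.50τ. This stands for a large effect. For 0.45 point the test stays weak even with all visits.

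A reader might also infer that 220 was sized for the year-1 comparison, so that no power is lost by relying on it. The reproduction is too loose and not unique: a crossover calculation with 0.56 read as HbA1c points gives about 190.

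**Conclusion.** The point holds in this form. The article expects the year-1 effect to persist, describes no washout, and still permits carry-over to be the first term removed from the model for its primary hypothesis. If it is removed, the pooled estimate varies with the maintained fraction under either reading of change. It lies between 0.50τ and τ for persistence between full and none on level or change from month 0, and between τ and 1.50τ if year-2 change starts at month 12.

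The bias formulas are algebra and need no assumption beyond the two-period model. The documents give no figure for f. The detection rates, average estimates and type I error rest on the assumed pre-test, 88 per arm, SD 1.8 and correlation 0.30, and show what could happen under one plausible use of the rule. The issue should be settled before analysis because it affects the headline estimate and can be resolved by wording.

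**What to change.** - Name the between-arm difference in HbA1c change from baseline at month 12, as randomised and from the already planned year-1 model (months 0, 6 and 12), as the primary estimate.
- Delete the sequential reduction rule for the primary analysis.
- Use year-2 data only for the maintenance aim and for a secondary description of the delayed arm, and do not test carry-over out of any model reported there.

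This changes text only. Both stated reasons for crossing over, maintenance and access for all, are still served. The price is the within-patient precision of the crossover contrast, which would be valid only without carry-over. Since 220 is only loosely reproduced, no claim is made that the stated power carries over to the year-1 comparison.

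### Two analyses are given primary status, and one of them, a joint analysis of all physiological outcomes, conflicts with HbA1c as the single powered primary outcome

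*Protocol article*

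**What the plan says.** Study Design sets the hierarchy: "The primary outcome is the change in HbA_1c_ level". The next sentence reads "Secondary outcomes include changes in blood pressure and LDL cholesterol levels". Sample Size Justification agrees: "The sample size calculation is powered to detect the primary outcome, which is the change in HbA_1c". It uses HbA1c inputs only, "with a SD of 1.8 and an effect size of 0.56 for aim 1".

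Data Management and Analysis then describes two analyses.

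- For the primary hypothesis it extends the usual crossover analysis with a time trend over year 1 and states that "we will regard subjects as a random effect and will use Gaussian mixed model estimation". The same section says of clustering that "we will include random effects in the model for clinic site, PCP, and HC".
- The following paragraph opens: "The primary analysis of all physiological outcomes jointly in the repeated measures design will be conducted using a general linear model framework". Repeated-measures MANOVA is then brought in to explore effects on several correlated outcomes. Stepdown F tests and discriminant function analysis serve as post hoc tests to find which outcomes were affected.

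The article does not rank the two analyses, and it does not list the outcomes that enter the joint one.

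**The concern.** The primary label is attached both to a model for the primary hypothesis and to a joint analysis of every physiological outcome. The two have different null hypotheses. The HbA1c model asks whether treatment changes HbA1c. The joint test asks whether treatment changes anything in the set, and the follow-up tests then look for what moved.

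The two can disagree in both directions. The joint test can be significant because blood pressure, lipids or weight moved while HbA1c did not. It can also miss an effect confined to HbA1c that the single-outcome test would detect. With no stated order, the deciding test could be chosen after the results are known.

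**Working it through.** **1. What the sample size was built for.** Inputs from Sample Size Justification: SD 1.8, effect size 0.56, cross-time correlation 0.30 with compound symmetry, ICC 0.01, 5 clusters, design effect 1.34, two-sided alpha 0.05, power 80%, dropout 20%, N = 220.

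- Design effect: 220 × 0.8 = 176 completers and 176 / 5 ≈ 35 per cluster, so 1 + (35 − 1) × 0.01 = 1.34. This reproduces.
- N with 0.56 in SD units: 4 × (1.96 + 0.8416)² / 0.56² = 100.1 in total, and 100.1 × 1.34 / 0.8 = 168 (171 if each arm is first rounded up to 51).
- The same with change-score variance 2(1 − 0.30) = 1.4: 140.2 × 1.34 / 0.8 = 235, or 140.2 × 1.34 × 1.2 = 226.
- N with 0.56 in HbA1c points (0.56 / 1.8 = 0.311 SD): 324.4 × 1.34 / 0.8 = 544.

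The scale of the effect size and the model are not stated, so 220 is neither confirmed nor refuted. The stated inputs describe HbA1c alone; none belongs to a multivariate test.

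**2. Power of a joint test if only HbA1c moves.** I take one change value per patient per outcome, two equal arms and a two-group MANOVA (Hotelling T²). Power comes from the noncentral F with p and N − p − 1 degrees of freedom and noncentrality λ = (N/4) × δ′S⁻¹δ, where δ holds the standardised effects and S the correlations. For a fair comparison, N is set where HbA1c alone has 80% power: at d = 0.56 this is 102 effective patients, λ = (102.07 / 4) × 0.3136 = 8.00. With uncorrelated outcomes and an effect on HbA1c only, λ stays at 8.00 while p rises:

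| Outcomes in the joint test | Power |
|---|---|
| 1 (HbA1c) | 80% |
| 3 | 64% |
| 4 (HbA1c, systolic, diastolic, LDL) | 58% |
| 6 | 50% |
| 8 | 44% |

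**3. The same four-outcome test under other assumptions.** The article gives neither the correlations nor the effects on the other outcomes, so both are assumed. All effects are coded in the direction of improvement.

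| Correlation | Effect on each of the other three (SD) | Power |
|---|---|---|
| 0 | 0 | 58% |
| 0 | 0.3 | 87% |
| 0 | 0.56 | over 99% |
| 0.3 | 0 | 67% |
| 0.3 | 0.3 | 64% |
| 0.5 | 0 | 81% |
| 0.5 | 0.3 | 58% |

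The joint test can therefore do worse or better than the 80% test. The article does not allow one figure to be chosen.

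**4. A positive joint test with no HbA1c effect.** Take four uncorrelated outcomes, no effect on HbA1c, and one secondary outcome that moves by d. With 176 completers, λ = 44 × d²; with the design effect, N = 176 / 1.34 = 131.3 and λ = 32.8 × d².

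| d of one secondary outcome | Joint test significant, N = 176 | N = 131.3 |
|---|---|---|
| 0.3 | 31% | 23% |
| 0.4 | 53% | 40% |
| 0.5 | 75% | 60% |

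The sizes of d are assumptions. That the joint test rejects without any HbA1c effect follows from its null hypothesis and does not depend on them.

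**The case against.** The strongest defence is that HbA1c's status is plain everywhere else. The Abstract, Introduction, Study Design and Sample Size Justification all call it primary. The mediation analyses are triggered by an HbA1c benefit over usual care, not by a joint test. The disputed sentence could also mean only the main approach within the joint analysis. This defence stands to the extent that HbA1c is not clearly replaced. It does not remove the conflict, because the sentence still calls a joint analysis primary and the article never says which analysis decides.

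Four stronger readings are tempting, and the article does not support them.

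- *That MANOVA is the primary analysis.* The label is attached to the joint general linear model. MANOVA is described as exploratory, its follow-up tests as post hoc, and a further set of MANOVAs as secondary.
- *That incomplete patients are discarded.* Classical repeated-measures MANOVA does need complete vectors. However, the section plans intention-to-treat with imputation and keeps complete cases for an additional per-protocol analysis. A figure for the share with complete vectors would also need a missed-visit rate that the article does not give.
- *That the joint test always costs power.* The Objectives expect blood pressure and LDL to improve too, so an effect on HbA1c alone is not the trial's own expectation. Under some such assumptions the joint test gains power.
- *That the planned random effects for site, PCP and HC cannot be fitted.* Classical MANOVA does not carry them, but the mixed model can, and the article refers to them only as part of the model.

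**Conclusion.** The point holds as a contradiction within the article. Two analyses carry primary status, and the joint one does not match the single outcome that is named primary and powered. What is certain is the difference in hypotheses: a significant joint test does not imply an HbA1c effect, and N was not derived for such a test.

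The size is conditional. Where HbA1c alone has 80% power, the four-outcome joint test ranges from 58% to over 99% across the assumed correlations (0 to 0.5) and assumed effects on the other outcomes (0 to 0.56 SD). The 58% is the case of an HbA1c-only effect with uncorrelated outcomes and should not be quoted as the general loss. The calculation also assumes one summary value per outcome, and the number of outcomes is itself not fixed in the article.

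A full analysis plan may already rank the analyses. The article as published still states two primaries and needs correcting.

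**What to change.** State that the mixed-model treatment contrast for change in HbA1c, in all randomised patients, is the single primary analysis that decides the trial. Analyse blood pressure and LDL as secondary outcomes in the same model form. Remove the word primary from the joint analysis, and label the joint general linear model, the MANOVA, the stepdown F tests and the discriminant analysis secondary or exploratory.

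This costs only wording in the analysis section, to be settled before the outcome data are analysed. No change in N follows from it, and no planned analysis has to be dropped.
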